### Endpoints

The primary endpoint of the study will be the proportion of patients developing at least an irAE at week 48 after the initiation of ICI therapy. An irAE was defined as any symptom, sign, syndrome, or disease caused by an immune-activating mechanism during the administration of an ICI once other causes such as an infectious disease or tumor progression have been ruled out.

Key secondary endpoints will be irAE-free survival, progression-free survival, cancer-related survival and overall survival. Other secondary outcomes will be proportion of ICI withdrawal due to the occurrence of irAEs, time to autoantibody appearance and number of positive autoantibodies included in the panel at week 48 after the initiation of ICI therapy.

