### Follow-Up Methods

Once enrolled in the study, patients will be monitored following standard recommendations. In accordance with clinical practice guidelines (Schneider et al., 2021; Schneider et al., 2022), all patients will be assessed in a treatment planning visit at baseline. In this initial visit, attending physicians will take a detailed personal and family history focused on ADs, chronic infectious and organ-specific diseases, and conduct a physical examination. In addition, to guide their care, patients will undergo a baseline blood test including a complete blood count, measurement of glucose and thyroid stimulating hormone (TSH) levels and lipid profile, renal and liver function tests, coagulation tests, and serological tests for hepatitis B and C viruses and HIV.

The frequency of follow-up will depend on the treatment schedule of each specific ICI, discretion of the attending physician and occurrence of complications (irAEs, non-immune-related toxicity, infections). All patients will have direct telephone access to the investigators in order to report early symptoms potentially related to the occurrence of irAEs*.* Treatment schedules of the ICIs will be classified into every 2 or 3 weeks up to week 12; thereafter, drug administration may be spaced out to every 4 or every 6 weeks, respectively, according to the drug data sheets.

Two types of blood samples will be taken for research purposes only: ordinary samples, defined as those drawn routinely as scheduled (Figure 1 and Figure 2), and extraordinary samples, defined as those taken at the time an irAE is detected. As far as possible, ordinary blood samples will be collected at the same time as blood draws for medical purposes before the administration of each ICI dose, in accordance with the study schedules (Figures 1, 2).

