#### Ordinary Samples and Study Schedules

Prior to receiving the first dose of ICI, all patients will undergo a baseline (i.e., week 0) blood test for research purposes, at the same time as their baseline blood test for medical purposes.

For ICIs administered every 2 weeks (nivolumab, avelumab, and durvalumab), sequential blood tests will be performed per protocol at weeks 2, 6, 12, 24, 36 and 48 after ICI initiation, all of them at the same time as draws for medical purposes (Figure 1). In other words, four ordinary samples will be obtained in the first 12 weeks (i.e., at 0, 2, 6, and 12 weeks after ICI initiation). Thereafter, the ordinary blood sampling interval will be every 12 weeks up to the end of follow-up at week 48.

For ICIs or combinations of ICIs administered every 3 weeks (ipilimumab plus nivolumab, pembrolizumab, and atezolizumab), sequential blood tests will be performed at weeks 0, 3, 6, 12, 24, 36 and 48 after ICI initiation, all of them at the same time as draws for medical purposes (Figure 2). In other words, four ordinary samples will be obtained in the first 12 weeks (i.e., at 0, 3, 6, 12 weeks after ICI initiation). Thereafter, the ordinary blood sampling interval will be 12 weeks up to the end of follow-up at week 48.

In the event of a delay in the administration of an ICI dose due to any eventuality other than an irAE, the ordinary sample corresponding to that treatment cycle will not be obtained. If the delay is due to the occurrence of an irAE, then an extraordinary sample will be obtained, as per protocol (see “*Extraordinary samples*” in the next section). Once treatment resumes, the ordinary sample corresponding to that treatment cycle will be collected per protocol.

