### Variables

Patients included in the study will be identified by a numerical code. In this way, the data collected by researchers will not include personal information, safeguarding patient confidentiality. The transmission, processing, and dissemination of personal data from all the participating patients will be handled in accordance with Regulation (EU) 2016/679 of the European Parliament and of the Council of 27 April 2016 on the protection of natural persons regarding the processing of personal data and the free movement of such data, i.e., the General Data Protection Regulation.

Study data will be entered into an electronic database to which all participating hospitals will have centralized access, and which will comply with all data protection requirements.

Dependent variable: occurrence of irAEs.

An irAE is defined as any symptom, sign, syndrome, or disease caused by an immune-activating mechanism during the administration of an ICI once other causes such as an infectious disease or tumor progression have been ruled out.

Other descriptive variables related to irAEs:• Description of symptoms related to the irAE• Type: organ-specific or systemic (≥ 2 organs affected)• Description of the involved organ• Syndrome/disease: Sjögren’s syndrome, sarcoidosis, systemic vasculitis, systemic lupus erythematosus, etc.• Severity, according to Common Terminology Criteria for Adverse Events v. 5.0• Date of diagnosis of the irAE• Treatment used for the irAE: non-steroidal anti-inflammatory drugs, glucocorticoids, immunosuppressive drugs other than glucocorticoids• ICI dose reduction: yes/no• ICI withdrawal: yes/no; if yes: temporary/permanent.

Independent variables: the following potential predictors of irAEs will be collected and analyzed: Epidemiological data: date of birth, sex, ethnicity.

General clinical data:• Smoking and alcohol use• Comorbidities: arterial hypertension, hypercholesterolemia, diabetes mellitus, cirrhosis/liver failure, renal insufficiency, thyroid dysfunction• Chronic infections: hepatitis B, hepatitis C, HIV infection• Autoimmune diseases prior to ICI initiation• Type of previous autoimmune disease (description)• Eastern Cooperative Oncology Group performance status score• Body mass index (in kg/m^2^).

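### The sampling schedule and the week-48 outcome run on calendar weeks but the delay rules run on treatment cycles, so antibody measurements depend on dose interruption and irAE status

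*Protocol article*

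**What the plan says.** All places are in the protocol article.

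- **Schedule (Ordinary Samples and Study Schedules).** Both regimens are timed from the first dose. For two-weekly drugs, "sequential blood tests will be performed per protocol at weeks 2, 6, 12, 24, 36 and 48 after ICI initiation", in addition to the baseline draw. For three-weekly drugs, "sequential blood tests will be performed at weeks 0, 3, 6, 12, 24, 36 and 48 after ICI initiation". Sampling ends with follow-up at week 48.
- **Outcome (Endpoints).** One of the other secondary outcomes is the "number of positive autoantibodies included in the panel at week 48 after the initiation of ICI therapy". Time to autoantibody appearance is another.
- **Link to dosing (Follow-Up Methods).** "As far as possible, ordinary blood samples will be collected at the same time as blood draws for medical purposes", and these draws come "before the administration of each ICI dose, in accordance with the study schedules".
- **Delay rules (Ordinary Samples and Study Schedules).** If a dose is delayed for a reason other than an irAE, the ordinary sample of that cycle is not taken. If the reason is an irAE, an extraordinary sample is taken. The paragraph then ends: "Once treatment resumes, the ordinary sample corresponding to that treatment cycle will be collected per protocol".
- **Withdrawal (Variables).** The data collected include "ICI withdrawal: yes/no; if yes: temporary/permanent". Endpoints also lists the proportion withdrawn because of irAEs. No sentence says whether ordinary sampling goes on after ICI is stopped, and none says that it ends.

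**The concern.** The schedule and the outcome count weeks since the first dose, while the delay rules count treatment cycles. The two clocks agree only while dosing is uninterrupted. Once it is interrupted, the rule that applies depends on the cause of the delay, and that cause is the study's dependent variable: whether the patient has an irAE.

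Four secondary analyses use the serial samples:

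- the week-48 count of positive autoantibodies;
- time to autoantibody appearance;
- the comparison of patients positive before ICI, positive after ICI and never positive (Secondary Objectives);
- the repeated-measures analysis of variance over 48 weeks (Sample Size Calculation and Statistical Analysis), which in its classical form needs complete and aligned time points.

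A patient sampled less often has fewer chances to be found positive and is more likely to be classed as never positive. A patient sampled later has had more time to seroconvert by the same nominal week. If both features differ by irAE status, part of any antibody difference between the groups could come from the sampling rule. Samples that were not drawn cannot be recovered when the biobank is analysed.

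**Working it through.** **1. The plan's own figures.** The article gives no expected number of week-48 samples. Its sample size is 70 irAE cases, plus 70 × 0.75 / 0.25 = 210 patients without an irAE, total 280, and 280 × 1.05 = 294. No term in this depends on serial sampling, so N is not touched.

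**2. Do the clocks agree without delay?** Follow-Up Methods gives dosing every 2 or 3 weeks to week 12, then possibly every 4 or 6 weeks respectively. Under all four patterns (2 throughout, 2 then 4, 3 throughout, 3 then 6), each of weeks 0, 2 or 3, 6, 12, 24, 36 and 48 is also a dosing week. The schedule is coherent for an uninterrupted patient.

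**3. Number of samples after one delay on a sampling cycle.** The full schedule has 7 ordinary samples.

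| Patient | Ordinary | Extraordinary | Total |
|---|---|---|---|
| No delay, no irAE | 7 | 0 | 7 |
| One non-irAE delay | 7 − 1 = 6 | 0 | 6 |
| One irAE delay, interrupted cycle's sample drawn on resumption | 7 | 1 | 8 |

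The extraordinary sample is a deliberate feature and follows any irAE. The extra asymmetry from the delay rules is the ordinary sample: lost in one case, kept in the other.

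**4. Timing after an irAE hold of *d* weeks.** The cycle named in the resumption sentence can be read in two ways.

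- *The interrupted cycle.* Its sample is drawn *d* weeks late. With *d* = 8, the week-12 sample is drawn at 12 + 8 = week 20.
- *The cycle current at restart.* The sample may be on schedule, and the one that fell in the hold has no stated replacement.

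Under the first reading, and only if later cycles also keep their nominal labels, the week-48 sample falls at 48 + 8 = week 56. That is after follow-up ends, so it could be missing rather than late.

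**5. If samples stay on calendar weeks but are drawn before doses.** Take six-weekly dosing with a pause after about week 18. Pauses of 1, 2, 3, 4 and 8 weeks put the last dose by week 48 at weeks 43, 44, 45, 46 and 44. A pause of 6 or 12 weeks leaves a dose at week 48. Week 48 is therefore a dosing day only for some pause lengths, and no window is stated.

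**6. After ICI is stopped.** Both delay rules presuppose a further cycle, so neither secures the week-24, 36 or 48 sample. As an illustration only, assume no off-drug draws and 20% to 60% of the 280 evaluable patients off ICI by week 48. Then 280 × 0.80 = 224 down to 280 × 0.40 = 112 would have a week-48 sample. The documents give neither that share nor that rule.

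**The case against.** The strongest reply is that the main schedule is already a calendar schedule for the whole cohort, followed to week 48. The pre-dose link is only a preference, since the sentence opens with a qualifier ("As far as possible, ordinary blood samples will be collected at the same time as blood draws for medical purposes"), and patients off ICI still have care draws. The article condenses a fuller protocol and its schedule figures are not available here, so silence on sampling after withdrawal is weak evidence. The outcome named is also a minor one.

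Much of this stands. A reader might infer that ordinary samples simply follow the dosing cycle, so that patients off ICI have no week-48 measurement. The text does not say so. A reader might also put a size on it: with exponential ICI duration and medians of 16, 24 or 40 weeks, 0.5^(48/median) gives 12.5%, 25% or 43.5% still treated at week 48, hence about 56% to 88% unmeasured. That range needs assumed durations and a strict pre-dose rule that the article does not state. It also counts patients who have died, whom no sampling rule could measure. It is not evidence of the loss under this plan.

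The resumption sentence is ambiguous, as shown above. It might even be meant to cover both kinds of delay. In that case the asymmetry in ordinary samples would shrink, but drift from calendar time would extend to all delays.

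The delay rules themselves are not answered by this reply. They are stated rather than left out, they use a different clock from the schedule and the outcome, and they differ by the cause of the delay.

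**Conclusion.** The point holds in limited form. As written, the delay rules make the presence, number and timing of antibody measurements depend on dose interruption and irAE status. Late sampling after an irAE hold is one reading of the text; a shift of week 48 past the end of follow-up needs a further assumption. For patients who stop ICI, the finding is only that no stated rule secures the later samples, although none excludes them.

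The effect is confined to the secondary antibody outcomes listed above. The primary endpoint, baseline serology and N = 294 are unaffected. The share of patients concerned cannot be derived from the documents, so no overall size is claimed. The change is worth making because it is cheap and the loss cannot be repaired afterwards.

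**What to change.** Replace the delay rules in Ordinary Samples and Study Schedules, and align Follow-Up Methods with them:

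- Every post-baseline ordinary sample is due by calendar week from the first ICI dose, within a stated window. An example is ±2 weeks from week 12 on. The window needs to be narrower at weeks 2 or 3 and 6, because ±2 weeks around week 3 (1 to 5) overlaps ±2 weeks around week 6 (4 to 8).
- One rule applies whatever the cause of a delay.
- The sample is taken with any routine care draw, whether or not ICI is being given, up to week 48 or death.
- Extraordinary samples at irAE diagnosis remain as planned and stay labelled as such.
- Each sample is classified by its actual date. Only in-window samples count for the week-48 outcome, and the number of patients contributing is reported.

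The cost is protocol wording and, for a patient who stops ICI after week 12, up to three research draws (weeks 24, 36 and 48) that the weekly schedule already foresees. Some patients off ICI will not return, so coverage will be incomplete. The change concerns research sampling only and implies nothing about ICI dosing.

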#### Extraordinary samples

At the time an irAE is detected, an additional blood sample will be collected for tests including the autoantibody panel under study. At the discretion of the attending physician, screening for other more specific antibodies may be requested based on the clinical manifestations of the patient. For ethical and decision-making reasons, the results of these extraordinary analyses for medical purposes will be available to the attending physicians.

### Laboratory Management and Sample Circuit

Both ordinary and extraordinary samples for research purposes will be separated from samples for medical purposes and will be processed to obtain six 500-μL aliquots of serum each. These aliquots will be stored at −80°C and appropriately labelled and coded in the biobank of each participating center. Ordinary samples corresponding to baseline (week 0), week 24 and week 48 will be processed to obtain peripheral blood mononuclear cells (PBMCs), which will be stored in the biobank at −80°C as cell pellets for subsequent DNA and RNA extraction.

After completion of follow-up, serum samples will be centralized in a single autoimmunity laboratory located in the Central Laboratory of Araba University Hospital (Vitoria-Gasteiz) to be analyzed by a blinded team of physicians and technicians with extensive experience in clinical laboratory testing. The panel of autoantibodies under study (ANAs, RF, and ANCAs) will be used to screen the serum from the ordinary and extraordinary samples. In some cases, the serum from the extraordinary samples obtained at the time of an irAE diagnosis may be tested for other more specific autoantibodies, at the discretion of the attending physician. In addition, vitamin D levels will be measured as 25-hydroxycholecalciferol in the serum from ordinary samples at baseline and weeks 24 and 48.

### Patient Safety

The E6(R1) Guidelines for Good Clinical Practice of the International Council for Harmonization of Technical Requirements for Pharmaceuticals for Human Use defines an adverse event as any unfavorable and unintended sign (including an abnormal laboratory finding), symptom or disease, whether or not related to the investigational product. This includes events related to the product, or comparator, or to the procedures involved.

If a patient develops an irAE, the attending physician will proceed according to clinical practice guidelines (Brahmer et al., 2021). Depending on the severity of the irAE, the maintenance and temporary or permanent ICI withdrawal will be considered. Toxicity will be assessed individually for each specific irAE type.

### Variables

Patients included in the study will be identified by a numerical code. In this way, the data collected by researchers will not include personal information, safeguarding patient confidentiality. The transmission, processing, and dissemination of personal data from all the participating patients will be handled in accordance with Regulation (EU) 2016/679 of the European Parliament and of the Council of 27 April 2016 on the protection of natural persons regarding the processing of personal data and the free movement of such data, i.e., the General Data Protection Regulation.

Study data will be entered into an electronic database to which all participating hospitals will have centralized access, and which will comply with all data protection requirements.

Dependent variable: occurrence of irAEs.

An irAE is defined as any symptom, sign, syndrome, or disease caused by an immune-activating mechanism during the administration of an ICI once other causes such as an infectious disease or tumor progression have been ruled out.

Other descriptive variables related to irAEs:• Description of symptoms related to the irAE• Type: organ-specific or systemic (≥ 2 organs affected)• Description of the involved organ• Syndrome/disease: Sjögren’s syndrome, sarcoidosis, systemic vasculitis, systemic lupus erythematosus, etc.• Severity, according to Common Terminology Criteria for Adverse Events v. 5.0• Date of diagnosis of the irAE• Treatment used for the irAE: non-steroidal anti-inflammatory drugs, glucocorticoids, immunosuppressive drugs other than glucocorticoids• ICI dose reduction: yes/no• ICI withdrawal: yes/no; if yes: temporary/permanent.

Independent variables: the following potential predictors of irAEs will be collected and analyzed: Epidemiological data: date of birth, sex, ethnicity.

General clinical data:• Smoking and alcohol use• Comorbidities: arterial hypertension, hypercholesterolemia, diabetes mellitus, cirrhosis/liver failure, renal insufficiency, thyroid dysfunction• Chronic infections: hepatitis B, hepatitis C, HIV infection• Autoimmune diseases prior to ICI initiation• Type of previous autoimmune disease (description)• Eastern Cooperative Oncology Group performance status score• Body mass index (in kg/m^2^).

Data related to the tumour:• Tumour type• Date of diagnosis• PD-L1 expression in tumour cells (%)• Date of initiation of ICI therapy• Dates of ICI administration• Date of progression• Date of death• Progression-free survival, defined as time from start of ICI therapy to tumor progression, death or last day of follow-up• Overall survival, defined as time from start of ICI therapy to death or the last day of follow-up• Cause of death: cancer-related, non-cancer-related, ICI-associated toxicity (immune-related, non-immune-related adverse event, infection or other).

Data related to treatment received before ICI initiation:• Nonsteroidal anti-inflammatory drugs• Glucocorticoids• Other immunomodulatory drugs: e.g., colchicine, hydroxychloroquine, mesalazine, or sulfasalazine• Oral anticoagulants (acenocoumarol, low-molecular-weight heparin, direct oral anticoagulants).

Data related to ICI:• Type: anti-CTLA4 (ipilimumab), anti-PD1 (nivolumab and pembrolizumab), anti-PD-L1 (atezolizumab, avelumab, and durvalumab)• Monotherapy or combination therapy (description)• Adjuvant or palliative therapy, and if palliative, line of therapy (first line, second line, other).

Laboratory data:

Obtained from blood samples for care and research purposes:• Glomerular filtration rate (ml/min/m^2^), levels of glucose (mg/dl), bilirubin (mg/dl), alanine aminotransferase, aspartate aminotransferase, gamma-glutamyltransferase (U/L), and thyroid stimulating hormone (μUI/mL).• Prothrombin time (percentage) or international normalized ratio (INR)• Complete cell count: haemoglobin (g/dl), white blood cells (/µL), differential white blood cell count of neutrophils, lymphocytes, monocytes, and eosinophils (/μL) and platelets (/μL)• Lipid profile: levels of cholesterol, triglycerides, and high- and low-density lipoprotein cholesterol (mg/dl).

Obtained from blood samples only for research purposes:• 25-hydroxycholecalciferol (ng/ml) at weeks 0, 24 and 48.• Levels of the autoantibodies under study (i.e., ANAs, RF and ANCAs) in ordinary samples according to study schedules (Figures 1, 2) and extraordinary samples.

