Survival will be assessed using a Kaplan-Meier analysis and compared between groups using the log-rank Mantel-Cox test. A subgroup analysis according to tumour type and extent of cancer (local, advanced, and metastatic disease) will be performed to assess survival outcomes*.* A multivariate analysis using logistic regression and Cox regression will be performed to detect factors associated with the occurrence of irAEs. Applying a manual backward stepwise procedure, a multivariate model will be constructed from variables that either have a p-value of less than 0.10 in the univariate analysis or are considered relevant to the dependent variable on the basis of previous studies (e.g., sex and age of patients, type of ICI). Variables not reaching statistical significance will be dropped from the final predictive model. The sensitivity, specificity, positive predictive value, negative predictive value, and probability ratios with their corresponding 95% confidence intervals of the model will be calculated. The diagnostic accuracy of the predictive model inferred from the logistic regression model will be described with the area under the receiver operating characteristic curve.

Two-sided hypothesis tests will be performed, and the significance level will be set at 5%. The statistical analysis will be conducted using IBM SPSS Statistics software version 27.0 (Chicago, IL).

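### Study outcomes and measurements made after treatment start are listed as candidate predictors of irAEs, and the variable-selection rule does not exclude them

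*Protocol article*

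**What the plan says.** The Variables section of the protocol article first sets the outcome: "Dependent variable: occurrence of irAEs". It then gives a separate group of descriptive variables about the irAE, such as severity, treatment and ICI withdrawal. A third block holds the independent variables. It opens by announcing that "the following potential predictors of irAEs will be collected and analyzed", and it runs to the end of the section. Its sub-headings (tumour, earlier treatment, ICI, laboratory) sort the items by topic and do not change their role.

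Under the tumour sub-heading stand the dates of ICI administration, progression and death, together with three survival items:

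- PFS, counted from ICI start and ended by progression or death.
- OS, in these words: "Overall survival, defined as time from start of ICI therapy to death or the last day of follow-up".
- A classification of deaths in which one category is immune-related. It reads "Cause of death: cancer-related, non-cancer-related, ICI-associated toxicity (immune-related, non-immune-related adverse event, infection or other".

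Under the laboratory sub-heading stand "25-hydroxycholecalciferol (ng/ml) at weeks 0, 24 and 48" and autoantibody levels from both ordinary and extraordinary samples. Follow-Up Methods defines extraordinary samples as those taken when an irAE is detected.

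The Endpoints section names PFS, OS and cancer-related survival as key secondary endpoints. Secondary Objectives compares cancer-related survival between patients with and without irAEs. In Sample Size Calculation and Statistical Analysis, the selection rule is that "a multivariate model will be constructed from variables that either have a p-value of less than 0.10 in the univariate analysis"; the alternative route into the model is relevance shown in earlier studies. Backward selection follows, and then sensitivity, specificity, predictive values and AUC of the model.

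**The concern.** The same variables have two opposite roles. In the objectives and endpoints, survival is the outcome and the irAE defines the groups. In the variable list, survival is a potential predictor of the irAE. The selection rule does not resolve this, because it screens on a p-value alone.

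Both primary objectives are at stake: finding predictive factors of irAEs, and the diagnostic properties of the resulting model. A variable known only after the irAE, or one that reflects how long the patient was observed, cannot help a clinician at ICI start, yet it can raise the apparent AUC and sensitivity. The model is also meant to go on to external validation in an independent cohort, so the error would be carried forward.

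**Working it through.** **The plan's own figures.** 70 cases / 0.25 = 280 patients, of whom 210 have no irAE. 280 × 1.05 = 294, as stated. The point does not depend on this total; 280 and 25% are used below only as the setting.

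**When each listed item becomes known**

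| Item in the predictor list | Why it is not a valid predictor as listed |
|---|---|
| PFS, OS, dates of progression and death | Outcomes under Endpoints; tied to time at risk |
| Cause of death | The immune-related toxicity category implies that an irAE occurred |
| Dates of ICI administration | Follow-Up Methods allows for dose delay because of an irAE |
| Vitamin D at weeks 24 and 48 | May follow the irAE; week 48 is the endpoint date itself |
| Autoantibodies in extraordinary samples | Exist only in patients with a detected irAE |

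**Size of the effect for OS.** Assumptions, not taken from the documents: constant hazards, death and irAE independent, and 48-week survival S of 80%, 65% or 50%. With λd the death hazard and λ the irAE hazard per week:

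- λd = −ln(S)/48
- λ solves λ/(λ+λd) × (1 − exp(−48(λ+λd))) = 0.25, so that 25% have an irAE before death or week 48.

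Check at S = 0.80: λd = 0.2231/48 = 0.00465 and λ = 0.00676. Then 0.00676/0.01141 × (1 − exp(−0.548)) = 0.593 × 0.422 = 0.25.

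The share alive at week 48 is S(1 − exp(−48λ))/0.25 in patients with an irAE and S·exp(−48λ)/0.75 in those without. The last two columns come from 2,000 simulated studies of 280 patients, with a Mann-Whitney test of OS capped at week 48.

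| S | λ per week | Alive, irAE | Alive, no irAE | Passes p<0.10 | AUC of OS alone |
|---|---|---|---|---|---|
| 80% | 0.00676 | 88.7% | 77.1% | 78% | 0.56 |
| 65% | 0.00754 | 79.0% | 60.3% | 97% | 0.61 |
| 50% | 0.00861 | 67.7% | 44.1% | nearly 100% | 0.66 |

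A repeat with another random seed gave 77%, 97% and 99.9%, with AUC 0.56, 0.61 and 0.66. A variable with no relation to irAEs should pass in about 10% of studies and have an AUC of 0.50. The excess arises because a patient must stay alive to be observed having an irAE.

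**A measurement altered by the irAE.** Suppose a marker carries no information at baseline and the irAE then shifts it by δ standard deviations. Its AUC is Φ(δ/√2): 0.64, 0.76 and 0.86 for δ = 0.5, 1.0 and 1.5. The shifts are assumptions. In 500 simulated studies each, the marker passed the screen in 97%, 100% and 100%.

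**The case against.** The strongest reply is that this is a data inventory under a careless heading. It contains raw dates that nobody would enter in a regression. The roles of PFS and OS are clear elsewhere, the direct consequences of irAEs have their own list, and the examples given for the model are sex, age and type of ICI. The pilot model described in the Discussion used sex, age and autoantibody positivity. This has force: a drafting slip is plausible, and a reader who infers that the sponsor has decided to model irAEs on OS or cause of death goes further than the text. It does not remove the contradiction, because the article does label these items as predictors and its selection rule would admit them.

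Three other stronger readings are not supported either:

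- **Liver and thyroid tests.** They carry no time point in the list, and hepatitis and thyroiditis are irAEs, so a reader might infer that on-treatment values will be used. Follow-Up Methods describes a baseline draw with these analytes, and the exact time point may be left to the full protocol. This is not counted as an error.
- **OS as a consequence of the irAE.** The OS calculation does not show this. Death was made independent of irAEs, so the effect is one of time at risk.
- **Only week-0 variables anywhere.** A blanket rule would conflict with the study's own aims. Secondary Objectives and Table 1 include autoantibodies that develop on treatment, a Cox regression is planned, and Management of Confounding and Interaction Factors adjusts for concomitant glucocorticoids.

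**Conclusion.** The concern holds as a stated contradiction: outcomes and follow-up variables are named as candidate predictors of the event, and nothing in the selection rule keeps them out. The clearest items are cause of death and extraordinary-sample autoantibodies, since each presupposes an irAE in at least part of its content. Under the assumed 48-week survival of 80% to 50%, OS alone would pass the screen in 78% to nearly 100% of studies, with an AUC of 0.56 to 0.66 and no true link. At the favourable end the AUC distortion is modest. These figures apply only if OS is actually entered. The effect on sensitivity and on the selection of other predictors was not calculated. Because the plan as written bears on both primary objectives, it should be corrected before analysis.

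**What to change.** 1. In Variables, move dates of progression and death, PFS, OS, cause of death and dates of ICI administration to an outcome and follow-up list.
2. In Sample Size Calculation and Statistical Analysis, state that this list enters neither the univariate screen nor the irAE model.
3. For the logistic model and its AUC, restrict laboratory and vitamin D candidates to week-0 values. Keep vitamin D at weeks 24 and 48 as descriptive.
4. Let on-treatment measures (development of autoantibodies, concomitant glucocorticoid use) enter only as time-dependent covariates in the Cox model, using values from before the first irAE.
5. Exclude extraordinary-sample results as predictors. They can still serve the secondary objective on autoantibody appearance up to irAE diagnosis.

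The cost is a change of wording and the set-up of a time-dependent Cox analysis. No new data are needed, given that the planned glucocorticoid adjustment already presupposes a record of concomitant use, and the recruitment target stays at 294. The apparent AUC may be lower.
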